### Participant Characteristics

To achieve the aim of this study, it is desirable that the participant group is relatively homogenous with regard to health profile and disease risk factor presentation to ensure internal validity of the results. However, a broad representation of Australian adults according to demographic and social factors will be sought to improve generalisability of the study findings

for the community. The total number of participants with AD+CVD should not exceed a third of the sample size. Participants of each gender, a wide range of ages, ethnic and social backgrounds will be represented in this study.

### *Inclusion Criteria*

To participate in this study, participants must be:

- 40-85 years old\*;
- Outpatients diagnosed with either probable VaD as defined by the National Institute of Neurological Disorders and Stroke (NINDS) and the Association Internationale pour la Recherche et l'Enseignement en Neurosciences (AIREN) (Roman et al, 1993) or possible Alzheimer's Disease as defined by the National Institute of Neurological and Communication Disorders and Stroke (NINCDS)-Alzheimer's Disease and Related Disorders Association (ADRDA) (McKhann et al, 2004) with significant neuroimaging (CT or MRI) evidence of cerebrovascular disease;
- An MMSE score between 10 - 24 for the diagnosis of mild to moderate dementia;
- Absence of severe depression (Geriatric Depression Scale 15-item version, total score  $\leq 11$ );
- Stable or controlled by optimal medication over a minimum of 6 months if on cholinesterase inhibitors and 3 months for (if present) hypertension, diabetes, cardiac disease or stroke, or if on hypnotics and sedatives, stabilised for more than 3 months prior to inclusion in the study;
- Agreement to take part in the study as evidenced by a personally signed and dated informed consent document indicating that the subject (or a legally acceptable representative if the subject is unable to provide consent), has been informed of all pertinent aspects of the study;
- Participants must also be accompanied by a study partner/carer, and this person must be able to assist the participant comply with the study protocol. This requires the study partner/carer to be in contact with the participant at least 2 days per week;
- If female, has no intention to become pregnant during the study.

\* *Rule waiver:* a participant aged over 85 years may still be eligible for enrolment if he/she fulfils the following two conditions:

- (1) the participant meets all inclusion and exclusion criteria of the study;

(2) participant's health status is likely to allow for successful completion of the 15-month study based on clinical judgement of the principal investigator after assessing the participant's medical history, current health and comorbidities and factors potentially affecting compliance (e.g., availability of a reliable study partner/carer). A 9-point Clinical Frailty Scale (see Appendix 3) will be used to facilitate PI's decision making process. Clinical Frailty Scale is a well validated tool used clinically to predict death or need for institutional care in elderly (Rockwood et al., CMAJ, 2005; 173:489-495). The participant may be considered suitable for this study if his/her frailty score is less or equal to 5 (mildly frail). In such a scenario, a rule waiver will be completed before enrolment.

### *Exclusion Criteria*

Participants will be excluded from the trial if they:

- Have other types of dementia and/or severe form of delirium, depression, schizophrenia, acute illness or poorly controlled chronic diseases;
- Receive administration of the ingredients in the *SLT* formula (ginseng, ginkgo and saffron);
- Have a history of severe forms of peptic ulcers, diabetes with complications, pulmonary disorders, renal and/or hepatic disorders;
- Abnormal pathology test results: Cr > 1.5 times upper limit of normal (ULN); Alt, AST or ALP > 2 times ULN; PT > 3 second more than ULN; APTT > 10 seconds more than ULN; Plt < 100x10^9/L;
- Have a stroke in the 3 months before screening;
- Have severe dysphasia, mental retardation and/or life expectancy < 6 months;
- Are allergic to more than 2 medications or at least 1 ingredient of *SLT*;
- Are participating in another clinical trial;
- Are pregnant or lactating.

### *Additional Exclusion Criteria - MRI Sub-study*

- Allergy to Gadolinium contrast medium
- Pacemaker implanted;
- Have any wires, clips, or other metal implanted;
- Have a cochlear implant.

### **Discontinuation of Participants from Treatment or Assessment**

Should any of the above exclusion criteria present after enrolment of the study, the Investigator will be required to immediately contact the Chief Investigator to determine the next appropriate course of action.

Participants who enter the trial, finish their baseline examination, are allocated to randomised treatment and begin taking the blinded medication will be counted as withdrawal cases if, during the study if they:

- Become pregnant;
- Withdraw informed consent. Participants are free to discontinue their participation in the trial at any time, without prejudice to further treatment;
- Become lost to follow-up during the 52-week trial period;
- Demonstrate significant protocol non-compliance as determined by the investigator; or
- The Investigator considers that it is not in their interest to continue the study.

The study may be discontinued at any time by the sponsor or the Coordinating Chief Investigator on the basis of new information regarding safety or efficacy. Additionally, the study may be terminated if progress is unsatisfactory. Withdrawn/discontinued participants will not be replaced.

### **Procedures for discontinuation**

In case of premature termination or suspension of the trial, the coordinating chief investigator must inform the trial participants and ensure appropriate follow up and therapy. In addition, the regulatory authorities and ethics committee must be informed.

Participants may withdraw/discontinue from the study at will at any time without explanation. The participant may also be withdrawn at the discretion of the Investigator due to a safety concern or if judged non-compliant with trial procedures. Participants that withdraw/discontinue from the study will be asked to attend the end of treatment visit (Visit 8, Week 52) to monitor their safety, with a window period of up to 14 days of their withdrawal. The reason for withdrawal and date of withdrawal must be documented in the participant's source data file and electronic Case Report Form (CRF). All AEs and SAEs must be followed until resolution or stabilisation unless, in the Investigator's opinion, the condition is unlikely to resolve.

### **Concomitant Treatment**

Participants may take routinely prescribed medications provided the relevant condition has been stable or controlled by optimal medication for more than 3 months except those drugs prohibited by the Exclusion Criteria. For other medications (including herbal medicine and nutritional supplements), which may have cognitive effects (e.g., cholinesterase inhibitors, beta blockers, angiotensin receptor blockers), the doses should be stable for at least 6 months for ChE inhibitors and 3 months for all other medications prior to the commencement of the trial and remain stable for the duration of the study. The details of all medical treatments and health management plans will be recorded as part of the screening process and then, following enrolment, during every follow-up visit. Notification of a person's enrolment in the trial and the implications for management will be communicated, with their consent, to their General Practitioner. It is anticipated that the presence or effect of any existing treatment confounders or effect modifiers will be equally distributed between groups due to the randomisation process.

### **3.3 Study Protocol**

**Figure 3. Schematic Trial Protocol**

[figure not shown]

### Recruitment Protocol

Recruitment strategies to be used in the Australian sites will include:

- All clinicians involved in this trial and their associated hospitals, clinics and networks
- Advertising through Alzheimer's Australia website
- Visits by the investigators to major aged care outpatient and nursing home facilities
- Visits to Division of General Practice meetings/events
- Posters and brochures in aged care, general practices and other health facilities
- Recruiting through Step Up For Dementia Research website
- Media resources of Western Sydney University e.g. advertisements in local newspapers
- Advertising through newsletters and websites of NICM Health Research Institute (NICM), Western Sydney University
- Advertising through online social media platforms (e.g., twitter, Facebook, Instagram)

Resources required for the recruitment phase of the trial include advertising materials, Health Practitioners Information Packages (information sheets for practitioners, information sheets for administration staff, information sheets and contact cards for potential participants). Participants may also be directly mailed information about the trial. Participants can take as much time as is required to consider their participation.

### Screening Appointment Protocol

Based on our team's previous experience with recruitment rates for the VaD pilot trial, it is anticipated that 238 participants can be recruited over a 24 month period. The participants will be assessed and classified according to the NINDS-AIREN or NINCDS-ADRDA diagnostic criteria. Mini-mental Status Examination (MMSE) will also be recorded to distinguish types and severity of dementia. A sub-set of 50 participants will undergo Magnetic Resonance Imaging (MRI) scans. Other assessments will include: history and examination, blood tests for reversible dementia, Computer Tomography (CT) scans, and neuropsychological assessment if deemed necessary.

### Randomisation and Allocation Concealment Protocol

Randomisation will be conducted external to the primary research team (investigators listed at the start of this document) by a research officer of the National Institute of Complementary Medicine (NICM). This person will be responsible for producing computer generated randomisation treatment sequences which randomly associate a randomisation number with either active or placebo treatment. NICM's Clinical Trials Manager and Strategic Operations Manager are responsible for securely storing the randomisation allocation in a restricted access electronic file.

Randomisation numbers will be allocated in permuted blocks of 6 randomisation numbers starting from 001 to 238 with each block containing 3 active and 3 placebo assigned randomisation numbers. Sites will allocate the randomisation numbers in order of number sequence starting with the lowest number in each block and using all numbers in a block of 6 before starting with the next block of numbers. As soon as the randomisation number is assigned, it will be recorded on the screening log, in the participant source data file and electronic Case

Report Form (eCRF). Details of any participants randomised out of sequence will be notified immediately to the Coordinating chief investigator.

Investigators and/or pharmacists may request to break the blind for a participant if there is a clinical need to know the treatment allocation for a subject e.g. to manage the treatment of a serious adverse event. The site's Principal Investigator needs to discuss the reasons for breaking the blind with the Coordinating Investigator (or if unavailable, the Trial Coordinator). If this request is approved, it will be forwarded to the NICM Clinical Trials Manager. The NICM Senior Manager and Clinical Trials Manager will liaise with the Chief Investigator to process the code break request. When a participant allocation blinding is revealed, the participant ID, date, reason for opening, name of person and signature of who broke the seal, should be provided in writing. The Principal Investigator, Chief Investigator and Statistician will be notified of this information. The participants, principal investigators, research team members, trial medical practitioners, data collection nurses and other staff of the trial centres will have no knowledge of the randomisation assignments until follow-up outcome measures and data analysis are complete.

### MRI Substudy Protocol

Structural MRI, MRA and dynamic contrast enhanced (gadolinium) perfusion MRI, are performed on a GE 3 Tesla 750W wide bore scanner and 32-channel Nova head coil at Macquarie Medical Imaging (MMI). The following protocols will be completed within an hour session. Our structural scan (T1-weighted and FLAIR) protocols and diffusion scan protocols were developed in line with the proposal from the Alzheimer's Disease Neuroimaging Initiative (ADNI). The supervising neuroradiologist is [name] at MMI. Standardised protocol: 3D T1-weighted contiguous coronal sections through whole brain (T1-TFE sequence and 3D acquisition) with voxel size 1 x 1 x 1 mm^3; 3D T2-weighted FLAIR contiguous axial slices whole brain with voxel size 1 x 1 x 1 mm^3. Then we will perform susceptibility weighted imaging (SWI) for examining cerebral microbleeds. High directional (61-gradient directions) diffusion weighted imaging (DWI) will then follow. We will then carry out angiogram (MRA) scan before taking gd-perfusion scan which is for generating cerebral blood flow and volumes. We will then do a post-gadolinium enhancement volumetric T1-weighted (this has better grey/white matter contrast than the pre-gd T1-weighted). We have all these T1 and T2 volumetrics (including pre- and post-gd T1s) for an accurate estimation of brain volumetric

changes in 12 months. Images will be de-identified, and then transferred to a secure workstation at Centre for Healthy Brain Ageing (CHeBA), UNSW. This protocol will remain the same for the 12-month follow-up scans.

### Treatment Description

Shineway Pharmaceutical Co. Ltd. will be responsible for manufacture and container preparation of the two trial intervention agents. The preparations will be manufactured in China in accordance with Australian TGA (Therapeutic Goods Administration) GMP requirements and regulations.

#### GROUP 1

Active is *SLT capsule*, composition:

- Ginsenosides powder – 27.27 mg
- Ginkgo flavone glycosides–27.27 mg
- Crocins – 5.46 mg

Participants in Group 1 will take 2 *SLT capsules* (60 mg/capsule), twice daily for 52 weeks.

#### GROUP 2

Placebo capsules will be created by the same manufacturer (Shineway Pharmaceuticals) to have similar colour, taste, texture and weight and will have no constituents which provide therapeutic effects. Participants in Group 2 will take 2 placebo capsules, twice daily for 52 weeks.

### Medication Container Labelling Instructions

Each capsule container must state:

- Name of sponsor
- Pharmaceutical dosage form
- Batch/code number to identify contents and packaging operation (may be encoded for blinding purposes)

- Directions for use - take orally 2 capsules in the morning and 2 capsules in the evening with meals
- Statement “for clinical trial use only”
- A trial reference code
- Storage conditions
- Use-by or expiry date
- Statement “keep out of reach of children”

And any other items required to be consistent with TG048 (Therapeutic Goods Order TG048)

### **Clinical Laboratory Parameters and Abnormal Laboratory Test Results**

For participants recruited in the Australian centres, tests will be performed by a certified pathology laboratory. Hard copies of all results will be provided to the investigator and transferred electronically to the clinical database.

The following laboratory tests will be performed at Screening, Week 4, Week 13, Week 26, Week 39, Week 52/EOT and Week 65:

|                     |                                                                         |
|---------------------|-------------------------------------------------------------------------|
| Haematology         | Haemoglobin (Hb)                                                        |
|                     | Haematocrit (Hct)                                                       |
|                     | Red Blood Cell Count (RBC)                                              |
|                     | Platelets Count (Plt)                                                   |
|                     | White Blood Cell Count (including a five part differential in absolute) |
| Coagulation testing | Prothrombin time (PT)                                                   |
|                     | Activated Partial Thromboplastin Time (APTT)                            |
|                     | Fibrinogen (FIB) Level                                                  |
| Liver Function      | Total Bilirubin (TBil)                                                  |
|                     | SGOT (AST)                                                              |
|                     | SGPT (ALT)                                                              |
|                     | Alkaline Phosphatase (ALP)                                              |
|                     | Albumin (ALB)                                                           |
|                     | Total Protein (TP)                                                      |

|                |                           |
|----------------|---------------------------|
| Renal Function | Blood urea nitrogen (BUN) |
|                | Creatinine (Cr)           |
| Electrolytes   | Sodium (Na)               |
|                | Potassium (K)             |
|                | Chloride (Cl)             |

The results of all laboratory tests required by the protocol will be recorded in the participant's source data file and in the subject's CRF. All clinically important abnormal laboratory tests occurring during the study will be repeated at appropriate intervals until they return either to the subject's baseline (i.e. the level recorded at Screening) or to a level deemed acceptable by the investigator and the clinical monitor (or his/her designated representative), or until a diagnosis that explains them is made.

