### Secondary efficacy endpoints

The secondary efficacy endpoints of the study will be the differences between the *SLT* and the placebo groups in the changes between baseline and 26-, and 52-week follow-up visits in:

- Scores of Clinician's Interview Based Impression of Change-plus (CIBIC-plus)
- Scores of additional executive function tests including CLOX and EXIT-25 from Baseline and 26-, and 52-week follow-up visits
- Scores of DEMQOL from Baseline and 26- and 52-week follow-up visits
- Scores of *Neuropsychiatric Inventory-Clinician rating scale* (NPI-C) from Baseline and 26- and 52-week follow-up visits
- Changes in MRI biomarkers from Baseline and the end of treatment assessment (52 week follow-up)

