### **Baseline visit (Week 0)**

Participants who meet all of the inclusion and none of the exclusion criteria will be scheduled to return to the site for their Baseline visit. At Baseline, the following will be performed:

- Check of inclusion and exclusion criteria.
- Check concomitant medications and procedures and note any changes in the CRF.
- Complete assessment scales VaDAS-cog, ADCS-ADL, CIBIC-plus, DEMQOL, NPI-C, CLOX and EXIT-25
- Complete MRI scans for substudy (50 participants only).

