### 4.3 Implications for Participants

Each participant will be required to contribute time to visit the allocated trial centre on eight occasions over a 65-week period.

- Screening consultation
- Baseline consultation
- 2-week telephone review of adverse events
- 4-week review
- 13-week review
- 26-week review
- 39-week review
- 52-week review
- 65-week review

The first occasion will involve a comprehensive consultation and health check-up with the principal investigator and a medical practitioner responsible for trial screening (including establishment of the diagnosis). Participants who do not fully meet the inclusion criteria will not be included in the study and will be notified of this outcome and any abnormal findings/test results from the screening. Their family doctors may also be contacted if the nature of these findings warrants this.

Subsequent visits for review and medication collection will be briefer. On five occasions (not at 0 and 65-week review), the participants will be required to have a blood sample taken, which may involve brief discomfort but poses no significant health risks. Participants will need to refrain from caffeine and smoking on the morning before blood testing and avoid alcohol and exercise for 24 hours prior to testing. Participants will be reimbursed up to \$30 for travel expenses and/or the time spent at each visit. In accordance with the above-mentioned ethical guidelines, a placebo will be utilised in this trial because there is no currently effective alternative medication for treatment of VaD. In addition, participants will continue to take their current prescribed medication.

A subset of 50 participants will undergo MRI scans. MRI scanning does not cause any pain, and the magnetic fields are not known to produce tissue damage of any kind. Some participants may experience discomfort when in an enclosed space or may find the noise of the scanner during

testing loud. Earplugs will be provided to prevent problems with noise and participants are able to communicate with the technician throughout the procedure. These participants will also be reimbursed for their travel expenses to the MRI centre.

Participants will be insured for their involvement in clinical research through Western Sydney University.

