### Safety Measures

- *Liver and renal function, and routine haematological and coagulation (PT, APPT and fibrinogen) tests* will be conducted at baseline, 4, 13, 26, 39 and 52 weeks after the commencement of the treatment.
- All adverse events will be recorded at each visit, including those suspected to be related to the treatment (such as headache, dizziness, vomiting, allergy, etc) and any worsening of symptoms will be closely monitored. An assessment of the relationship between the adverse events or abnormal test results and the treatment will be made by the chief investigators and

trial physicians. An adverse event will be followed up until it resolves or for up to a month after the study is concluded. Serious adverse events (SAEs) will be immediately reported to the Human Research Ethics Committee granting approval and Suspected Unexpected Serious Adverse Reactions (SUSARs) to the TGA, in accordance with their guidelines. The causality of SAEs will be thoroughly investigated.

| Week                                                     | -2 to 0          | 0                                | 2  | 4  | 13 | 26 | 39 | 52            | 65               |
|----------------------------------------------------------|------------------|----------------------------------|----|----|----|----|----|---------------|------------------|
|                                                          | Screening | Baseline                  |    |    |    |    |    | End Tx | Follow up |
| Window                                                   |                  | 0                                | ±3 | ±7 | ±7 | ±7 | ±7 | ±7            | ±7               |
| Initial neurological assessment                          | X                |                                  |    |    |    |    |    |               |                  |
| Medical History                                          | X                |                                  |    |    |    |    |    |               |                  |
| Vital signs (HR, BP, Ht, Wt)                             | X                |                                  |    | X  | X  | X  | X  | X             |                  |
| Physical Exam                                            | X                |                                  |    |    |    |    |    |               |                  |

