| NINDS-AIREN diagnosis                                    | X                |                                  |    |    |    |    |    |               |                  |
| MMSE                                                     | X                |                                  |    |    |    |    |    |               |                  |
| GDS                                                      | X                |                                  |    |    |    |    |    |               |                  |
| Inclusion/Exclusion criteria                             | X                | X - checked before randomisation |    |    |    |    |    |               |                  |
| VaDAS-cog                                                |                  | X                                |    |    |    | X  |    | X             | X                |
| ADCS-ADL                                                 |                  | X                                |    |    |    | X  |    | X             | X                |
| CIBIC-plus                                               |                  | X                                |    |    |    | X  |    | X             | X                |
| NPI-C                                                    |                  |                                  |    |    |    | X  |    | X             |                  |
| CLOX                                                     |                  | X                                |    |    |    | X  |    | X             |                  |
| EXIT-25                                                  |                  | X                                |    |    |    | X  |    | X             |                  |
| DEMQOL                                                   |                  | X                                |    |    |    | X  |    | X             |                  |
| Haematology, coagulation, liver and renal function tests | X                |                                  |    | X  | X  | X  | X  | X             |                  |
| MRI scanning (if applicable)                             |                  | X                                |    |    |    |    |    | X             |                  |
| Adverse Events                                           |                  |                                  | X  | X  | X  | X  | X  | X             |                  |

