| Con meds and procedures                                  | X                | X                                |    | X  | X  | X  | X  | X             |                  |

|                                 |  |  |  |  |   |   |   |   |  |
|---------------------------------|--|--|--|--|---|---|---|---|--|
| Compliance, success of blinding |  |  |  |  | X | X | X | X |  |
|---------------------------------|--|--|--|--|---|---|---|---|--|

Table 1. Data collection timeline

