| 4.0 | Week 65 visits (assessment visits) | Face-to-face on-site assessment for safety, VADAS-Cog, ADLs, and CIBIC | 
The options include:
 
 
1) Verbally consenting to continuing to visit the trial centre for these assessments at the site where such visits are still permitted; COVID-19 safety check and protection measures must be taken as per Item 3.4
 
2) Verbally consenting to being assessed at a nominated community centre; COVID-19 safety check and protection measures must be taken as per Item 3.4
 
3) Verbally consenting to receive a home visit from assessors; COVID-19 safety check and protection measures must be taken as per Item 3.4
 
4) For the sites where both on site and home visits are not feasible, and/or participants are unwilling to attend in person, the possibility of using telehealth or videoconferencing to conduct these assessments will be explored
 
 | All Centres    | 
Centres will need to assess their current policies and procedures to determine appropriate action.
 
Researchers to obtain verbal consent to collect any data remotely and record this in the source visit notes.
 
For face-to-face visits: the assessors, participant and caregiver will thoroughly wash their hands and/or use hand sanitizer prior to and following a face-to-face visit. Masks and/or gloves to be used in line with local health advice. Centres will need to ensure PPE supplies are readily accessible if conducting face-to-face visits.
 
If unable to collect data, record as Not Done and explain why in the source notes.
 |

| . | Activity | Pre-COVID Status | Alternate Arrangements | Responsibility | Note/Action |
|---|----------|------------------|------------------------|----------------|-------------|
|---|----------|------------------|------------------------|----------------|-------------|

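### The visit schedules conflict: Table 1 has no baseline NPI-C for a change-from-baseline endpoint, and the protocol disagrees with itself on Week 65 adverse events and laboratory tests

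*Protocol*

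**What the plan says.** **NPI-C.** Section 1.3 (Secondary efficacy endpoints) defines a between-group difference in change for "NPI-C) from Baseline and 26- and 52-week follow-up visits". The Section 3.3 list for the Baseline visit agrees: "Complete assessment scales VaDAS-cog, ADCS-ADL, CIBIC-plus, DEMQOL, NPI-C, CLOX and EXIT-25". Appendix 4, items 3.0 and 3.2, also place the NPI among the Week 0, 26 and 52 assessments. The schedule in Section 5.1, "Table 1. Data collection timeline", marks NPI-C at Weeks 26 and 52 only.

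**Adverse events.** Section 5.1 (Safety Measures) states "All adverse events will be recorded at each visit". Section 4.2 has a standard health question put at each visit. Section 3.3 (Treatment Protocol) has adverse events monitored and reported in connection with the 65-week follow-up. Appendix 4, item 4.0, gives the normal content of the Week 65 visit as "Face-to-face on-site assessment for safety, VADAS-Cog, ADLs, and CIBIC". Table 1 marks adverse events up to Week 52, and the Week 65 visit list in Section 3.3 has three scales and two administrative items, with no adverse-event entry.

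**Laboratory tests.** Section 3.3 (Clinical Laboratory Parameters and Abnormal Laboratory Test Results) says "The following laboratory tests will be performed at Screening, Week 4, Week 13, Week 26, Week 39, Week 52/EOT and Week 65". The Table 1 row reads "Haematology, coagulation, liver and renal function tests | X | | | X | X | X | X | X", and its Week 65 cell is empty. Sections 4.2 and 5.1 end at Week 52, and the Week 65 visit list has no bloods. Section 4.3 tells participants: "On five occasions (not at 0 and 65-week review), the participants will be required to have a blood sample taken".

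**The concern.** Table 1 is an operative document. The Treatment Protocol section refers the reader to it for the assessment schedule, and a table of this kind is what sites and eCRF builders normally work from. Where it disagrees with the text, what gets collected depends on which page a site reads.

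The NPI-C gap has the clearest statistical consequence. A baseline score that was not taken cannot be obtained later. Table 1 shows no NPI-C at screening that could stand in for it. The last-value-carried-forward rule in Section 5.2 cannot supply a value that precedes all the others. For such a participant the change defined in Section 1.3 does not exist.

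For Week 65 the risk is an uneven record. If some sites ask about adverse events or draw blood and others do not, an absent event cannot be told apart from a question that was not asked, and a rate for the off-treatment period would be hard to interpret. Week 65 is also the point after which 12 months of trial medication may be supplied, subject to investigator judgement.

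**Working it through.** No power or alpha calculation bears on this. The check is to set the schedules side by side and count.

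| Item | Source | Time points |
|---|---|---|
| NPI-C | Section 1.3; Baseline, Week 26 and Week 52 visit lists | 0, 26, 52 (3) |
| NPI-C | Table 1 | 26, 52 (2) |
| Adverse events | Sections 4.2 and 5.1, every visit | includes 65 |
| Adverse events | Treatment Protocol; Appendix 4 item 4.0 | follow-up monitoring; Week 65 includes safety |
| Adverse events | Table 1 | 2, 4, 13, 26, 39, 52 |
| Adverse events | Week 65 visit list | none |
| Laboratory | Clinical Laboratory Parameters | Screening, 4, 13, 26, 39, 52, 65 (7) |
| Laboratory | Table 1 | Screening, 4, 13, 26, 39, 52 (6) |
| Laboratory | Sections 4.2 and 5.1 | baseline, 4, 13, 26, 39, 52 (6) |
| Laboratory | Section 4.3, after the first visit | 5 occasions, Week 65 excluded |
| Laboratory | Week 65 visit list | none |

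**The plan's own figure.** Section 4.3 states five blood samples after the first visit. Table 1 gives 6 − 1 (screening) = 5, at Weeks 4, 13, 26, 39 and 52, so the two agree. The Clinical Laboratory Parameters section gives 7 − 1 = 6. The only time point in that list and not in Table 1 is Week 65.

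**NPI-C.** The Table 1 row is complete across nine visit columns, with Screening and Week 0 blank. The six scales around it (VaDAS-cog, ADCS-ADL, CIBIC-plus, CLOX, EXIT-25, DEMQOL) all carry a Week 0 mark. The gap is one missing mark: 3 required visits against 2 shown.

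**Adverse events.** The lists for Weeks 2, 4, 13, 26, 39 and 52 each include adverse-event recording; the Week 65 list is the only post-baseline one that does not. Because that list repeats the Table 1 omission, correcting Table 1 alone would leave a conflict with Sections 4.2 and 5.1. The document is also not uniform on scope: Section 1.1 has safety assessed over both intervention and follow-up, while the safety objective in Section 1.2 refers to 52 weeks.

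**Direction of each conflict.** For NPI-C, Table 1 stands alone against the text. For adverse events, Table 1 and the Week 65 visit list stand against four places. For laboratory tests, the Clinical Laboratory Parameters section stands alone against Table 1, the Week 65 visit list and Sections 4.2, 4.3 and 5.1.

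**The case against.** The strongest reply is that these are small inconsistencies in a protocol whose intent can be read. Baseline NPI-C is required by the endpoint definition, the Baseline visit list and Appendix 4, and nothing says it is not collected. A site would have to disregard its own visit list to miss it. Even then, randomised groups could still be compared on Week 26 and Week 52 scores. This largely stands and limits the size of the problem. It does not remove it: the endpoint as defined is a change, and the table to which sites are referred omits what is needed to compute it.

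On adverse events, the duty to capture them after Week 52 appears repeatedly. The section on procedures for discontinuation also has events followed to resolution or stabilisation, and Section 5.1 follows an event for up to a month after the study. This too has weight. Following known events, however, does not by itself prompt a site to ask about new ones at Week 65, and the visit list does not tell it to.

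On laboratory tests, the Week 65 entry may simply be stray, in which case no planned data are at risk. That is possible, and the documents do not decide it. During post-trial supply there are telephone calls every three months, an adverse-event diary and further pathology tests (narrowed by Appendix 4, item 4.2, under the COVID-19 contingency). These safeguards are real, but they apply after Week 65 and do not document Weeks 52 to 65.

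A reader might infer three stronger things:

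- **Table 1 is wrong throughout.** It is not: on Week 65 bloods it agrees with most of the text.
- **NPI-C change is lost for all 238 participants.** That is a ceiling, reached only if every site or the eCRF followed Table 1 over the Baseline visit list. The documents do not show this.
- **20% of follow-up (13/65 weeks) has no safety data.** That ratio is a length of time, not an estimate of missing data.

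**Conclusion.** The contradictions are real and should be corrected. Baseline NPI-C is missing from Table 1 and required elsewhere. Week 65 adverse-event recording is called for in four places and absent from the two that sites use as a checklist. Week 65 laboratory tests are scheduled in one section and unlisted or excluded in five places.

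The effect is bounded. It reaches one secondary endpoint and the off-treatment safety record, and only where a site or the eCRF follows the conflicting passage. The primary endpoints, the sample size and the primary analysis are not affected. How many participants are exposed cannot be estimated from the protocol, because the eCRF and site practice are not visible. The conclusion assumes only that Table 1 is used as a working schedule, which the protocol's own reference to it supports.

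**What to change.** 1. Add the Week 0 mark for NPI-C to Table 1. This restores what Section 1.3 and the Baseline visit list already require.
2. Reconcile Week 65 adverse-event recording and laboratory tests so that one schedule stands across Table 1, the Week 65 visit list, Clinical Laboratory Parameters, Treatment Protocol, Sections 4.2, 4.3 and 5.1, and Appendix 4 item 4.0. Which Week 65 safety schedule is intended is for the investigators to decide. Whatever is chosen, Section 4.3 should state the matching number of blood samples.
3. Align the eCRF with the reconciled schedule and send sites a short note. If participants have already been enrolled, check whether any lack a baseline NPI-C and report the number.

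The NPI-C correction adds no assessment beyond those already planned. The Week 65 reconciliation is a text change, with at most one additional blood sample and one adverse-event enquiry per participant relative to Table 1, depending on the choice made.
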